### Ethical Considerations

This study received approval on January 31, 2024, from the Institutional Ethics Committee of Datta Meghe Institute of Higher Education and Research (DMIHER(DU)/IEC/2024/137) to ensure adherence to ethical guidelines, respect participant rights, and meet established standards. This study has been registered with the Clinical Trials Registry-India under registration CTRI/2024/05/066865. Participants will be provided with an informed consent form, clearly describing the study’s aim, procedures, risks, benefits, and their right to opt out at any time. Consent for publication of data will be obtained and will be used for all analyses, including secondary analyses. We will confirm that the original consent and institutional review board approval explicitly cover the use of primary and secondary data. We ensure that the data collected will be fully anonymized, with no personally identifiable information retained or linked to any participant. As there are no interventions involved and as only a cross-sectional survey will be conducted in which the data will be collected via an interview and anthropometric measurements, participants will not be provided with any compensation in this study.

### Inclusion and Exclusion Criteria

Cases will be defined as children who are stunted, reside in the study area, are aged 6 months to 5 years, with a mother or father as the caregiver, reside in a household with or without livestock, and are willing to participate and follow the requirements of the study. Controls will be defined as children who are not stunted, residents of the same study area, aged 6 months to 5 years, with a mother or father as the caregiver, who reside in a household with or without livestock, and are ready to participate and follow the requirements of the study. Children will be excluded from the study if they exhibit any obvious congenital defect, have a major medical condition, or need a prolonged hospital stay after birth. Those who have not lived in the Wardha district for at least the past 3 months and those presently involved in another study on animal husbandry will also be excluded.

### Sample Size

The study will involve participants chosen based on specific inclusion and exclusion criteria. It will include all children younger than 5 years from the respective villages. Considering the overall number of children younger than 5 years in the Wardha rural area sample, the total population was 88,224 children [20].

Estimated sample size = n≥(NZ_(1-α⁄2)^2 p(1-p))/(d^2 (N-1)+Z_(1-α⁄2)^2 p(1-p)), where α (a)=.05; estimated proportion of children younger than 5 years who are stunted (height-for-age) *P*=.28 [9]; and estimation error (d) = 5% = 0.05. The minimal sample size calculated for this study will be 614, of which 307 are cases and 307 are controls, considering the ratio of case-control is 1:1.

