## Introduction

Stunting, which refers to low height/length for age, is usually a result of chronic undernutrition, often linked to poor socioeconomic conditions, maternal health, infant care, and children’s nutrition. It restricts children from achieving maximum physical and cognitive capabilities [1]. In 2022, 149 million children younger than 5 years experienced stunted growth, which accounts for 22.3% of all children younger than 5 years globally [2]. More than a million child deaths are estimated annually due to stunting, which is defined as a height-for-age below minus 2 *z* scores of the median height-for-age in the World Health Organization (WHO) child growth standards [3]. Stunting and undernutrition continue to have a high prevalence globally.

In India, although there has been economic growth and significant decreases in child mortality rates, undernutrition and stunting are still prevalent [4]. For children, stunting, wasting, and underweight are crucial markers of their nutritional condition. Although wasting results from acute food scarcity and illness, stunting is due to recurring illnesses and long-term inadequate nutritional intake. Stunting has generally irreversible impacts on delayed motor development and decreased cognitive development. However, wasting is a major indicator of death and needs to be addressed right now. Underweight integrates weight for length/height and linear growth hindrance data [1].

One of the key priorities for the 2030 “Zero Hunger” Sustainable Development Goal is reducing stunting [5]. Stunting and wasting are also highlighted in the Global Hunger Index 2017 report, in which India ranked 100th [6]. The latest National Family Health Survey-5 (NFHS-5) was conducted in India from 2019 to 2021, which revealed that underweight, wasting, and stunting are common in Indian children younger than 5 years. The prevalence of underweight, wasting, and stunting according to NFHS-5 was 35.5%, 19.3%, and 32.1%, respectively [7]. This is undoubtedly lesser than that reported in the NFHS-4 study, which was performed between 2015 and 2016 [8]. The stunting and wasting rate for Maharashtra as per recent NFHS-5 (2019-2021) was 35.2% and 25.6%, respectively. As per NFHS-4 (2019-20) from the district fact sheet of Wardha, Maharashtra, the stunting rate for rural children younger than 5 years was 29.4%, and the wasting rate was 25.8% [9].

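### The stated minimum of 614 does not follow from the printed planning proportion of .28, nor from the 29.4% that the article reports from the same reference (minor)

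*Protocol article*

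**What the plan says.** The Sample Size section uses a single-proportion precision formula with a finite population correction. Its inputs are:

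- the proportion, described as "estimated proportion of children younger than 5 years who are stunted (height-for-age) *P*=.28 [9", that is, cited to reference 9;
- an absolute error of 0.05, printed directly after the proportion ("P*=.28 [9]; and estimation error (d) = 5% = 0.05"), and a two-sided alpha of .05;
- the population: "children younger than 5 years in the Wardha rural area sample, the total population was 88,224 children [20", that is, cited to reference 20.

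The section calls the result minimal: 614 children, 307 cases and 307 controls, at a 1:1 ratio.

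The Introduction draws on reference 9 as well: "the stunting rate for rural children younger than 5 years was 29.4%, and the wasting rate was 25.8% [9". It introduces that source with the words "As per NFHS-4 (2019-20) from the district fact sheet of Wardha, Maharashtra". Earlier in the same section it dates the rounds differently: "NFHS-4 study, which was performed between 2015 and 2016 [8" for the fourth round, and "NFHS-5) was conducted in India from 2019 to 2021" for the fifth.

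**The concern.** One reference is the source of two different stunting proportions, .28 and .294. The text does not say why they differ or which population the .28 describes. Because the population count in the formula is the rural one, a reader would expect the rural rate beside it. The survey label does not help to sort this out: it joins the name of the fourth round to years that fall within the fifth.

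The proportion is the local input that drives the result, since the population is so large that the finite correction removes only about one child. Below 50%, a higher proportion gives a larger minimum. What is at stake is whether the figure called the minimum can be traced to the inputs printed beside it. Neither the design nor the analysis depends on the answer.

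**Working it through.** **Inputs.** N = 88,224, d = 0.05, p = .28 (Sample Size); z = 1.96 for two-sided alpha .05; alternative p = .294 (Introduction, reference 9).

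**Formula (the article's own).** n = N z² p(1−p) / [d²(N−1) + z² p(1−p)]. Here d²(N−1) = 0.0025 × 88,223 = 220.5575 and z² = 3.8416.

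**Step 1. The plan's figure at its printed p = .28.**
p(1−p) = 0.28 × 0.72 = 0.2016; times z² = 0.77447.
n = 88,224 × 0.77447 / (220.5575 + 0.77447) = 308.7, rounded up to 309.
Doubled for 1:1: 618. The stated figures are 307 and 614, so they are close (2 per group, 4 in total) but not equal, and they lie below the bound. Without the finite correction n is 309.8, rounded up to 310, so leaving out the correction does not explain the difference.

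**Step 2. The rural rate from the Introduction, p = .294.**
p(1−p) = 0.294 × 0.706 = 0.207564; times z² = 0.79738.
n = 88,224 × 0.79738 / (220.5575 + 0.79738) = 317.8, rounded up to 318.
Doubled: 636. The stated 614 is 22 lower (22/636 = 3.5%), or 11 per group.

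**Step 3. Which p gives 307?**
Solving n = 307 gives p = 0.2775, and solving n = 306 gives p = 0.276. Values from just above .276 up to about .2775 therefore round up to 307. All of them would print as .28 to two decimals.

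| p | n | Rounded up | Doubled | Minus stated 614 |
|---|---|---|---|---|
| about .276 to .2775 (not printed) | above 306, to 307 | 307 | 614 | 0 |
| .28 (Sample Size) | 308.7 | 309 | 618 | 4 |
| .294 (Introduction) | 317.8 | 318 | 636 | 22 |

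The other under-5 stunting rates for India and Maharashtra in the Introduction do not give 307 either: 32.1% gives 334 and 35.2% gives 350.

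**Step 4. The survey label.** The Introduction puts the fourth round in 2015 to 2016 and the fifth in 2019 to 2021, then attributes the Wardha figure to the fourth round in 2019-20. Either the round or the years are wrong, and the article alone does not show which.

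**The case against.** The strongest reply is that nothing printed shows .28 to be wrong. The Sample Size section does not call the proportion rural; that word belongs to the population count, which comes from another reference. A district fact sheet could hold both a rural rate of 29.4% and a whole-district rate near 28%, and 307 is just what an unrounded proportion of about .276 to .2775 would give. This stands. It means that the article cannot be said to use a false proportion.

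The reply also holds that the effect is trivial. For a simple prevalence estimate from 307 children, the margin would be 5.01 points at .28 and 5.09 at .294. It adds that the 636 arises only by doubling, a step that the text implies through the 1:1 ratio but does not justify. Both remarks are fair, and they are why the point is minor.

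A reader might go further and infer that the study is short by 22 children and must enrol more. The documents do not support that. The 22 depends on .294 being the intended input, which only reference 9 can settle. Moreover, cases and controls are sampled 1:1, so the stunted proportion in the sample is fixed at 50%, and a margin for stunting prevalence describes nothing that this sample estimates.

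What remains is that a figure presented as the calculated minimum cannot be obtained from the inputs printed with it, and that the one rate the article reports from the cited source gives a different figure.

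**Conclusion.** The point holds as a minor error of consistency and traceability. The stated 307 per group and 614 in total follow neither from the printed .28 (309 and 618) nor from the 29.4% reported from the same reference (318 and 636). The gap is 2 to 11 children per group, or 4 to 22 in total. The survey label on the source contradicts the dates in the same section.

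This rests on the article's own formula, z = 1.96, rounding up because the formula is written as a lower bound, and doubling for the 1:1 ratio. Reference 9 was not available, so the conclusion is that the article does not show where its figure comes from. It does not show that .28 is incorrect or that 29.4% must replace it. Whether a prevalence formula suits a case-control comparison is a separate question, and correcting the proportion would not answer it.

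**What to change.** - Check reference 9. State in the Introduction which survey round and years it covers, and correct the label.
- In Sample Size, say whether the proportion is the rural or the whole-district rate, and print it to the precision used in the calculation. Use the rate that matches the rural population, or justify another.
- Restate the calculated minimum from that value: 618 if the proportion is exactly .28, 636 if it is .294, 614 if an unrounded value between about .276 and .2775 is confirmed.
- If 614 is kept without such a value, call it the fixed planned size instead of the calculated minimum.
- Do not add a statement of the precision achieved for stunting prevalence, because the 1:1 sampling fixes the stunted proportion.

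The cost is two corrected sentences and one recalculated figure. Enrolment, fieldwork and analysis do not change.

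### The sample-size calculation is a one-sample prevalence-precision formula that gives about 309 children; it does not justify 307 cases plus 307 controls for the livestock–stunting odds ratio

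*Protocol article*

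**What the plan says.** The Protocol article, Sample Size, gives the formula as "Estimated sample size = n≥(NZ_(1-α⁄2)^2 p(1-p))/(d^2 (N-1)+Z_(1-α⁄2)^2 p(1-p)". Its inputs follow in the same section:

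- population: "the total population was 88,224 children"
- significance level: "where α (a)=.05"
- expected proportion: "estimated proportion of children younger than 5 years who are stunted (height-for-age) *P*=.28 [9]"
- precision: "estimation error (d) = 5% = 0.05"

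The section concludes: "The minimal sample size calculated for this study will be 614, of which 307 are cases and 307 are controls", with the 1:1 case-to-control ratio as the only explanation of the split. It names no livestock ownership rate, no odds ratio to detect and no power.

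The Objective and the Data Analysis section set a different target. The exposure is livestock ownership, measured by the TLU score. The outcome is stunting, which defines case status. The result is an odds ratio with a confidence interval, adjusted by multivariable logistic regression.

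The Introduction cites the same reference for another figure: "the stunting rate for rural children younger than 5 years was 29.4%, and the wasting rate was 25.8% [9]".

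**The concern.** A case-control sample size should follow from how common the exposure is among controls, the odds ratio worth detecting, the significance level and the power. None of the last three kinds of input for an association (exposure prevalence, odds ratio, power) enters this calculation. The one proportion that does enter is stunting prevalence, and the 1:1 design sets the stunted share of the 614 at 50% whatever the prevalence is.

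Two things are at stake. Readers cannot tell from the article which size of association the study could detect. And because 614 is presented as a calculated minimum, a non-significant TLU result could be taken as evidence of no association from an adequately sized study. That outcome is realistic: the Discussion describes one cited study with a small effect size and a cohort that found no relationship with child growth. The conclusions are meant to inform policy.

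**Working it through.** **Step 1. Reproduce the plan's own figure.** Inputs, all from Sample Size: N = 88,224; p = 0.28; d = 0.05; z = 1.96 (two-sided 5%).

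n = N z² p(1−p) / [d²(N−1) + z² p(1−p)]

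- z² p(1−p) = 3.8415 × 0.28 × 0.72 = 0.7744
- numerator = 88,224 × 0.7744 ≈ 68,324
- denominator = 0.0025 × 88,223 + 0.7744 = 221.33
- n = 68,324 / 221.33 = **308.7, so 309**

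**Step 2. Look for a route to 614.**

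| Variant | n |
|---|---|
| no finite-population correction | 310 |
| 90% confidence | 218 |
| 99% confidence | 532 |
| p = 0.294 | 318 |
| p = 0.5 | 383 |

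None gives 614. As a single total, 614 would need d of about 0.0354 instead of 0.05. Doubling does come close: 2 × 309 = 618, and 307 per group is within 2 of 309. A p of about 0.277 gives 306.7, so 307. The likely route is therefore a one-sample result used once for cases and once for controls.

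**Step 3. Does the formula support the doubling?** No. Its n is the whole of one random sample in which stunted and nonstunted children occur as they fall. Nothing in it describes a comparison of two groups.

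**Step 4. What 307+307 delivers for a yes/no ownership exposure.** Assumptions: ownership among controls p0 = 30%, 50% or 70% (the article gives none), two-sided 5%, unadjusted, independent children. With p1 = OR·p0 / (1 − p0 + OR·p0) and p̄ = (p1 + p0)/2:

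power = Φ{ [ |p1 − p0| − 1.96 √(2 p̄(1−p̄)/307) ] / √[(p1(1−p1) + p0(1−p0))/307] }

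Example, p0 = 0.5 and OR = 0.63: p1 = 0.315/0.815 = 0.3865; difference 0.1135; pooled SE 0.0401; unpooled SE 0.0398; power = Φ[(0.1135 − 0.0786)/0.0398] = Φ(0.88) = 81%.

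| Ownership in controls (assumed) | OR at 80% power | Power at OR 0.7 | Power at OR 0.8 |
|---|---|---|---|
| 30% | 0.59 or 1.61 | 49% | 23% |
| 50% | 0.63 or 1.58 | 59% | 28% |
| 70% | 0.62 or 1.69 | 55% | 25% |

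**Step 5. What it delivers for TLU as a continuous score.** Assuming an approximately normal score with equal SD in both groups, the detectable standardised difference is (1.960 + 0.842) × √(2/307) = 2.802 × 0.0807 = 0.226. The odds ratio per SD is exp(0.226) = 1.25, or 0.80 in the protective direction.

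**The case against.** **The doubling is visible.** The article prints the 307/307 split and the 1:1 ratio beside the total, so the like-for-like comparison is 307 against 309, which is trivial. This stands. The defect is the method and the unsupported doubling, not a slip in evaluating the formula. A reader might infer from 309 against 614 that twice too many children are planned. The documents do not support that, because the formula does not size a case-control comparison at all.

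**The 28% may be legitimate.** The Introduction's 29.4% is a rural figure. Sample Size cites 28% to the same reference without saying whether it is rural or total. The source could hold both, so a contradiction is not shown. What remains is a request to say which figure it is.

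**Prevalence may come from a wider set.** Sample Size says all under-fives of the villages are included, and Study Design has children sorted by stunting status after measurement. A prevalence might be estimated from everyone measured. That is possible, so it would be too strong to say the study cannot estimate prevalence. The point holds only for the 614: a sample fixed at 1:1 by stunting status does not by itself estimate it.

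**An article condenses the full protocol.** This does not answer the point. The article prints a complete calculation with inputs and result, and offers it as the basis for 614.

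**Conclusion.** The point holds as a fault in the sample-size method. The printed formula gives about 309 children for one prevalence estimate; 614 appears to be about twice that, and neither number bears on the odds ratio the study tests.

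A reader might go further and conclude that the study is underpowered. The documents do not establish that, since they give no target odds ratio and no ownership rate. Under the assumed 30–70% ownership, 307 per group is adequate for odds ratios of roughly 0.6 or below, or 1.6 to 1.7 and above, and weak for odds ratios of 0.7 to 0.8.

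These figures are best-case. They ignore the sampling of children by village, the multivariable adjustment and the restriction to participants with no missing data, all of which would generally make the detectable effects larger.

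**What to change.** Keep the planned 307 cases and 307 controls. Remove the prevalence formula and the description of 614 as a calculated minimum. State instead what the size delivers, for example:

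> *With 307 cases and 307 controls, two-sided alpha .05, unadjusted and assuming independent children, 80% power corresponds to an odds ratio of about 0.59 or 1.61, 0.63 or 1.58, and 0.62 or 1.69 if 30%, 50% or 70% of controls own livestock (assumed values). For TLU as a continuous score it is about 1.25 (or 0.80) per SD, assuming an approximately normal score. Village clustering, covariate adjustment and complete-case exclusions would generally make the detectable effects larger.*

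If the stunting proportion is still used elsewhere, such as the allocation across blocks, state which figure from reference [9] the 28% is, given the 29.4% rural rate in the Introduction.

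Cost: one section reworded and no extra participants. Data collection is planned from November 2025, after the article's publication date, so the statement can be corrected before results exist. The downside is that the stated justification becomes less favourable, because the detectable effects are moderate to large.

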### Data Collection Tools and Methods

Villages from all 8 blocks of Wardha district will be randomly selected using a computer-based randomization method. A list of all children younger than 5 years will be collected from the Anganwadi Center of the respective villages. The children will be selected from the list according to the inclusion and exclusion criteria. The final list of the selected children of respective villages will be arranged according to the location and proximity of their homes, and the investigator will visit their homes for data collection and anthropometric measurements. Data will be collected using a semistructured questionnaire in English/Marathi. The questions will be asked to the informant (either of the parents). The questionnaire will contain questions related to the sociodemographic profile of the child, mother, and household; personal history of the child; livestock ownership; livestock management and disease; environment; and behavioral determinants such as Water, Sanitation, and Hygiene (WASH) (Multimedia Appendix 1). Following the interview, the child’s height and weight will be measured. The digital weighing scale (Seca), pretested for accuracy, will be used to record weight with minimal clothing. Children up to the age of 2 years will have their length measured while lying on the horizontal measuring scale (Seca infantometer). Children older than 2 years will have their height measured with a stadiometer (Prestige). Height measurement will be conducted up to the nearest tenth of a centimeter. The child will have to stand on the scale barefoot, with heels together and shoulder blades, buttocks, and heels touching the vertical surface. The child’s height will be measured by placing a headpiece on the top of their head while they are looking straight ahead and their arms are hanging naturally at their sides. To ensure anthropometric accuracy, the data collectors will undergo 3-day training and standardization sessions following WHO protocols. Technical errors of measurement will be calculated before the study and will be monitored periodically. There will also be regular supervisory visits, which will ensure consistency and interrater reliability. To reduce recall and selection biases, there will be validation assessments utilizing anthropometric data and health records. Moreover, data triangulation will be utilized by combining interviews, focus groups, and observations from the community.

To calculate the total number of livestock, a standardized unit must be used to represent the livestock counts for all species. A TLU is a standard unit that allows for the comparison of various species of varying sizes by using a common measure. Conversion equivalents of livestock into TLU are mentioned in Table 1 for households with livestock ownership [21].

**Table 1 table1:** Conversion equivalents of livestock into Tropical Livestock Unit [16].

Species (animal type)	Tropical Livestock Unit equivalent
Cattle (bull)	1.0
Cattle (cow/buffalo)	0.8
Cattle (calves)	0.2
Sheep/goats	0.1
Horses	0.8
Donkeys/mules	0.5
Poultry	0.01

### Data Analysis

All the results will be calculated using RStudio software (version 4.3.2; Posit). The complete analysis dataset will consist of all study participants who have no missing data for any of the variables in the dataset. The study participants will be those individuals who meet the criteria for inclusion and exclusion. Baseline characteristics will be utilized to compile all the data, representing demographic variables with mean and standard deviation for continuous data and frequency and percentage for categorical data. The results will be examined for continuous data, which will be described using the minimum, maximum, average, standard deviation, standard error, and 95% CI for parametric data. The normality of the continuous outcome variables will be assessed initially with the Kolmogorov-Smirnov test at a 5% significance level (*P*≤.05). If the data are not rejected, a nonparametric test will be used to determine significance; otherwise, it will be considered normal. The significant difference at the 5% level (*P*≤.05) between stunted and nonstunted comparative groups will be determined using a 2-sided *t* test. Nonnormal data will be summarized using mean, median, and lower and upper quartiles for nonparametric testing and will be assessed for significance using the Mann-Whitney test. Categorical variables will be presented with frequency (n) and percentage value (%). The categorical variables (stunted and nonstunted) will be analyzed by Fisher exact test to find significant associations of different risk factors. All confounding variables will be analyzed using multivariable logistic regression. Associated risks will be investigated and tabulated using the odds ratio with a confidence interval. To understand the effects of multiple factors, confounding variables will be recognized and adjusted to understand the multiple factors that can influence the outcome (stunting). For the confounding effect, multivariable methods will be employed to estimate the association between exposure (livestock) and outcome (stunting), or the impact of one or more confounding factors such as WASH; wealth index of the household; episodes of illness; dietary habits; knowledge, attitude, and practices regarding livestock; and livestock diseases will be considered. Essentially, multivariable logistic regression will allow assessing the independent effect of each of the exposures.

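### The analysis set demands complete data on every variable in the dataset, so gaps in items that no model uses remove children; depending on coding, it could also remove households without livestock

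*Protocol article*

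**What the plan says.** The Data Analysis section names a single analysis set: "The complete analysis dataset will consist of all study participants who have no missing data for any of the variables in the dataset". The reference is to the dataset, not to the variables of a given model. The article names no other analysis set.

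Four other statements bear on how this rule would work:

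- **Inclusion and Exclusion Criteria:** cases and controls alike may "reside in a household with or without livestock", so non-owners are part of the design.
- **Data Collection Tools and Methods, questionnaire content:** besides sociodemographic items and the child's history, it covers "livestock ownership; livestock management and disease; environment" and behavioural determinants.
- **Data Collection Tools and Methods, TLU:** "Conversion equivalents of livestock into TLU are mentioned in Table 1 for households with livestock ownership". The value for a household with no animals is not stated.
- **Data Analysis, adjustment:** among the possible confounders, "knowledge, attitude, and practices regarding livestock; and livestock diseases will be considered".

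The Sample Size section gives a minimum of 614 children, 307 cases and 307 controls, from a formula with no term for incomplete records.

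**The concern.** A complete-case rule normally applies to the variables of the analysis in question. Applied to the whole dataset, it makes every item a condition for being analysed at all. A child with known stunting status, known livestock holdings and all model covariates would be discarded because an unrelated answer is blank. The longer the questionnaire, the greater the loss, and nothing is gained in return.

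The second issue concerns the exposure contrast. A household without animals has no animal disease or husbandry to report. If those fields are stored as missing, every non-owner fails the completeness test. Restricting the rule to model variables would not by itself solve this, because livestock disease is one of the named adjustment variables and a complete-case logistic regression containing it would drop the same households. Livestock ownership is the exposure in the title and the aim, so the comparison at stake is the main one.

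**Working it through.** **1. The plan's own figure.** The Sample Size formula is n = N·Z²·p(1−p) / [d²(N−1) + Z²·p(1−p)], with N = 88,224, Z = 1.96, p = 0.28 and d = 0.05.

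- Z²·p(1−p) = 3.8415 × 0.2016 = 0.7744
- d²(N−1) = 0.0025 × 88,223 = 220.56
- n = 88,224 × 0.7744 / (220.56 + 0.7744) = 308.7, rounded up to 309; doubled, 618

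This is close to the stated 307 and 614 (p = 0.277 gives exactly 307 and 614). What matters here is that no input allows for records dropped as incomplete.

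**2. Loss from ordinary gaps.** The article gives neither the number of variables (k) nor the missingness per variable (m), so both are assumptions. If gaps are independent across items, expected complete records = 614 × (1−m)^k.

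| Missing per item (assumed) | k = 10 | k = 20 | k = 40 | Difference, 10 vs 40 |
|---|---|---|---|---|
| 0.5% | 584 | 555 | 502 | 82 |
| 1% | 555 | 502 | 411 | 144 |
| 2% | 502 | 410 | 274 | 228 |

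For example, 0.99^10 = 0.904 gives 555 and 0.99^40 = 0.669 gives 411. Taking 10 as a plausible number of model variables and 40 as a plausible number of questionnaire variables, the last column shows the part of the loss that comes from applying the rule to the whole dataset. At 1% it is 144 children, or 144/614 = 23% of the planned sample. Since standard errors scale roughly with 1/√n, confidence intervals on the log-odds scale would be about √(555/411) = 1.16 times as wide.

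**3. Loss of non-owners, if inapplicable items are stored as missing.** Only owners would then remain. The share of owning households is not given. At assumed shares of 30%, 50% and 70%, the set would keep 614 × 0.30 = 184, 614 × 0.50 = 307 and 614 × 0.70 = 430 children before any other loss. At every share the number of unexposed children is zero. The owner versus non-owner odds ratio could then not be estimated, and only variation in TLU among owners would be left. That consequence needs no assumption about the ownership share, but it does depend on the coding.

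**4. Sections side by side.** The eligibility criteria deliberately admit non-owners. The questionnaire and the adjustment list include items that only owners can answer in full. The completeness rule makes no exception for items that do not apply. The three can be reconciled only by a coding rule, and the article does not give one.

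**The case against.** The strongest reply is that an inapplicable item is not ordinarily regarded as missing. The questionnaire is in Multimedia Appendix 1, which is not shown and may carry a not-applicable code, and such coding is a detail an article may leave to the full protocol. Admitting households without livestock as both cases and controls signals that the authors mean to keep them. Knowledge and attitude items can be put to non-owners, and the confounder list is introduced as examples to be considered, not as a fixed model. All of this stands. A reader might infer that the plan does exclude non-owners; the article supports only that the rule would do so under one way of coding.

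Two other stronger readings also fail:

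- **That fewer than 614 children are bound to be analysed.** Loss occurs only if values are missing, 614 is given as a minimum, and recruitment is not capped there. Data come from home interviews followed by measurement, so gaps can be limited at source. What holds is that no allowance is shown.
- **That the odds ratio will be biased because missingness follows wealth or maternal education.** In logistic regression, the complete-case exposure odds ratio can remain valid when missingness depends only on covariates in the model, and the wealth index is a named covariate. Bias would need missingness depending jointly on stunting and exposure, or on a relevant factor left out of the model. The article gives no evidence of either.

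The loss figures are also illustrative. Blanks tend to cluster within respondents, so independence probably overstates the number of children lost.

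None of this answers the main point. The dataset-wide rule is a stated choice, not an omission, and it is wider than any analysis needs.

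**Conclusion.** The rule is badly fixed and should be narrowed. As written, a gap in an item that no model uses removes the child from every analysis, and the sample size has no stated margin for that. The size of the loss is unknown. With independent 1% missingness, the dataset-wide rule would cost about 144 of 614 children beyond what a 10-variable model loses (555 against 411 retained); across 0.5% to 2% the excess runs from 82 to 228. These figures rest on assumed item counts, assumed rates and independence.

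The loss of the unexposed group is a conditional risk. It follows if livestock-specific items are left blank for non-owners and those blanks count as missing, and the documents do not show whether they would. It deserves a sentence in the plan because the consequence would be losing the main comparison. The point is a correction to the completeness rule; it does not show that the study's comparison is already lost.

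**What to change.** Replace the dataset-wide rule with completeness defined per analysis. Suggested wording:

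> Each analysis will include all eligible children with known stunting status, known livestock exposure and complete data on the covariates of that analysis. Households without livestock will have a TLU of 0. Items on livestock management and disease will be coded as not applicable, not as missing, in these households, and will be analysed among owning households only or with a separate non-owner category.

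Report the number analysed for each model. Multiple imputation of model covariates, with complete cases on the model variables as the alternative or as a sensitivity analysis, is a reasonable option but is not needed to correct the error.

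The cost is a change of wording, a modest amount of programming in R and slightly different denominators across analyses. No extra data are needed. The Results section plans data collection from November 2025, so the not-applicable code is best settled before forms are entered.
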